## **6.2. Pretreatment Assessments**

### **6.2.1. Screening Visit**

Prospective subjects should be screened no more than 28 days prior to administration of the first dose of the study drug. If the subject does not begin the treatment phase within this 28-day window, all Screening evaluation procedures must be repeated. Screening labs may be repeated once within 28 days prior to administration of the study drug to rule out laboratory error, in the opinion of the investigator.

A sufficient number of subjects will be screened to identify up to 100 subjects for enrollment in Parts A and B and, as necessary, an additional 50 subjects in Part C.

Subjects should be instructed to fast (no food or drink except water, for at least 10 hours), starting from 10 PM (22:00) or earlier, as appropriate, on the evening prior to the Screening visit to ensure an approximate 10-hour fast prior to the fasted blood sample collection the next morning.

Written informed consent must be obtained from each subject before the initiation of any Screening procedure. After a subject has provided informed consent, the investigator and other study personnel will determine if the subject is eligible for participation in the study. This assessment will include a review of the inclusion/exclusion criteria and completion of all Screening procedures as outlined in [Table 5](#) (for SAD cohorts) and [Table 6](#) (for MAD cohorts) and described in the following text.

Eligible subjects meeting all inclusion criteria and none of the exclusion criteria will be instructed on all protocol requirements, including the restrictions on concomitant medication usage and other substances as well as consumption of food or beverages containing alcohol, caffeine, or xanthine. Subjects will be asked to arrive at the study center on Day -1 (for SAD cohorts) and Day -2 (for MAD cohorts) for admission assessments.

From the time of obtaining informed consent through the first administration of the study drug, record all SAEs, as well as any AE related to protocol-mandated procedures on the AE eCRF. All other untoward medical occurrences observed during the Screening period, including exacerbation or changes in medical history, are to be captured on the medical history eCRF. See [Section 7](#) Adverse Events and Toxicity Management for additional details.

### **6.2.2. Admission Assessments**

#### **6.2.2.1. Admission**

Subjects meeting all eligibility criteria following the Screening evaluation will return to the clinic for admission assessments on Day -1 (for SAD cohorts) and Day -2 (for MAD cohorts). The admission evaluations and/or procedures are outlined in [Table 5](#) and [Table 6](#).

Prior to randomization on Day -1, the results of Screening clinical and laboratory evaluations (as described in [Table 5](#) and [Table 6](#)) must be reviewed by the investigator to confirm the continued

eligibility of each subject to participate in the study. At the time of randomization, subjects will be assigned a sequential subject number as described in Section 5.1. Subjects will remain confined to the study clinic for the duration as described in Section 6.2.2.2 and Table 5 or Table 6, as appropriate.

#### 6.2.2.2. Clinic Confinement

Following Screening and admission procedures, eligible subjects will be confined to the study center beginning at admission (Day -1 for SAD cohorts; Day -2 for MAD cohorts) until the completion of assessments on Day 4 (SAD cohorts) or Day 17 (MAD cohorts).

### 6.3. Check-In Assessments

Following confirmation of study eligibility at Admission, eligible subjects will be randomized to receive TLC-2716 or PTM starting on Day 1 and assigned a subject number and study drug administration time. Note, for MAD cohorts, regardless of randomization outcome, all subjects will receive PTM corresponding to the dose to be evaluated in the planned cohort on Day -1.

Study procedures and assessments are outlined in Table 5 (for SAD cohorts) and Table 6 (for MAD cohorts).

### 6.4. Treatment Assessments

Study procedures and assessments are outlined in Table 5 (for SAD cohorts) and Table 6 (for MAD cohorts).

### 6.5. Pharmacokinetic Assessments

PK assessments following single- or multiple-dose study drug administration, including but not limited to the following plasma PK parameters of TLC-2716 and its metabolites will be calculated as appropriate:

$AUC_{last}$ ,  $AUC_{inf}$  (single-dose),  $AUC_{tau}$  (multiple-dose),  $\%AUC_{exp}$  (single-dose),  $C_{max}$ ,  $T_{max}$ ,  $C_{last}$ ,  $T_{last}$ ,  $C_{tau}$  (multiple-dose),  $\lambda_z$ ,  $CL/F$ , and  $t_{1/2}$ .

#### 6.5.1. Plasma PK Collection

##### SAD Cohorts in Parts A and C:

PK sampling will occur relative to the morning dosing of TLC-2716 or PTM at the following time points for each cohort:

Day 1: Pre-dose ( $\leq 10$  minutes prior to dosing), 0.25, 0.5, 1, 1.5, 2, 2.5, 3, 3.5, 4, 6, 12, 24, 48, and 72 hours post-dose

### **MAD Cohorts in Parts B and C:**

Day 1: Pre-dose ( $\leq 10$  minutes prior to dosing), 0.25, 0.5, 1, 1.5, 2, 2.5, 3, 3.5, 4, 6 and 12 hours post-dose

Days 3, and 7: Pre-dose ( $\leq 10$  minutes prior to dosing), 2, and 4 hours post-dose

Day 14: Pre-dose ( $\leq 10$  minutes prior to dosing), 0.25, 0.5, 1, 1.5, 2, 2.5, 3, 3.5, 4, 6, 12, 24, 48, and 72 hours post-dose

***If in any MAD cohort in Part C, BID administration is evaluated, PK assessments should be performed at the following time points.***

Day 1: Pre-dose morning ( $\leq 10$  minutes prior to dosing), 0.25, 0.5, 1, 1.5, 2, 2.5, 3, 3.5, 4, 6, and 12 hours post morning dose (12-hour time point collected prior to evening dose)

Days 3 and 7: Pre-dose morning ( $\leq 10$  minutes prior to dosing), 2, and 4 hours post morning dose

Day 14: Pre-dose morning ( $\leq 10$  minutes prior to dosing), 0.25, 0.5, 1, 1.5, 2, 2.5, 3, 3.5, 4, 6, and 12 hours post morning dose (12-hour time point collected prior to evening dose), 12.5, 13, 14, 16, 18, 24, 48, and 72 hours post-dose

Every effort should be made to collect PK samples at the scheduled time point.

Plasma concentrations of TLC-2716 (and its metabolites, as applicable) will be determined and other PK parameters evaluated, as appropriate. Sampling time points may be modified by the sponsor based on emerging data and assay feasibility.

For all cohorts, a single PK sample will be collected at the ET visit, if applicable.

### **6.6. Pharmacodynamic Assessments**

Relevant PD biomarkers including measures of DNL, ANGPTL3, a comprehensive serum lipid profile (e.g., LDL-C, HDL-C, TG, ApoB), and other exploratory markers, will be determined and evaluated.

Serum lipids will be evaluated on safety lab collections in the fasting state prior to the standard morning meal and study drug dosing, with the exception of 12 hours post-dose on Day 1 following the first administration of study drug or PTM, as outlined in [Table 5](#) (for SAD cohorts) and [Table 6](#) (for MAD cohorts).

Dose and/or exposure-response relationships for LXR inverse agonism by TLC-2716 will be evaluated.

#### **6.6.1. Plasma and/or Serum Pharmacodynamic Assessments**

Blood samples will be collected to measure PD biomarkers for TLC-2716 at the time points described below, where '0' indicates the pre-dose time point in the morning. Blood samples for PD assessments will be collected in the same subject order on each day, including the pre-dose

day, in each cohort. For MAD cohorts, the collection times on the day prior to the dosing day (e.g., Day -1) must match those on the days of subsequent dosing ( $\pm 5$  minutes).

**SAD Cohorts in Parts A and C:**

Day 1: Pre-dose ( $\leq 10$  minutes prior to dosing) and 4 hours post-dose

**MAD Cohorts in Parts B and C:**

Day -1: (all  $\pm 5$  minutes of Days 1, 7, and 14 time points), 0, 2, 4, 6, and 12 hours

Days 1, 7, and 14: Pre-dose ( $\leq 10$  minutes prior to dosing), and 2, 4, 6, and 12 hours post-dose

All post-dose timings above are relative to the morning dose for QD or BID dosing. In the case of BID dosing in Part C, the 12 hours post-dose time point must be collected prior to the second daily dose of the study drug.

Sampling time points may be modified by the sponsor based on emerging data and assay feasibility.

**6.6.2. Stool Pharmacodynamic Assessments**

All stools, if available, will be collected once over approximately 24-hour intervals to measure PD and other exploratory biomarkers for TLC-2716 at the time points described below.

**SAD Cohorts in Parts A and C:** None

**MAD Cohorts in Parts B and C:** Single sample collections

Day -1: One specimen will be collected between Day -2 Admission and Day 1 (0, pre-dose)

Day 14: One specimen will be collected between time point 0 (pre-dose) and 24 hours post-dose

**6.6.3. Biomarker Assessments**

***Additional Biomarker Assessments***

To support evaluation of the effects of TLC-2716 on cholesterol and lipid homeostasis, a separate serum aliquot will be collected for potential exploratory biomarker assessments, including but not limited to IDOL, apolipoprotein C and E, and NMR-based lipid particle profiles.

Whole blood samples will also be collected to measure ABCA1 and ABCG1 mRNA expression, at the time points described below, where '0' corresponds to the immediately pre-dose time point in the morning on Day 1 or later as applicable. Blood samples for biomarkers will be collected in the same subject order on each day, including the pre-dose day, in each cohort. The collection times on Day -1 must match the time of the collection on the day of dosing time points ( $\pm 5$  minutes).

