### **Additional Biomarker Assessments**

To support the evaluation of the effects of TLC-2716 on lipid homeostasis, a separate serum aliquot will be collected for potential exploratory biomarker assessments, including but not limited to inducible degrader of low-density lipoprotein (IDOL), apolipoprotein C and E, and nuclear magnetic resonance (NMR)-based lipid particle profiles.

Whole blood samples will also be collected to measure ABCA1 and ABCG1 mRNA expression, at the time points described below, where '0' corresponds to the immediately pre-dose time point in the morning on Day 1, or later as applicable. Blood samples for biomarkers will be collected in the same subject order on each day, including the pre-dose day (for MAD cohorts), in each cohort. The collection times on Day -1 in MAD cohorts must match the time of the collection on the day of dosing time points ( $\pm 5$  minutes).

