Within Part A and SAD cohorts in Part C, initiation of single-dose administration at escalating dose levels will be determined by evaluation of cumulative safety data, and available and relevant PK and PD data up to and including Day 4, following single-dose administration of the previous dosing cohort. Similarly, in MAD cohorts in Parts B and C, initiation of multiple-dose administration at a higher dose level will be determined by evaluation of safety and available PK and PD data from all subjects enrolled through Day 14 of the previous dosing cohort. Additionally, in adaptive cohorts in Part C, sentinel dosing will be utilized in any cohort wherein the total daily dose to be administered is greater than has previously been evaluated. In these multiple-dose cohorts, to support a comprehensive evaluation of the relationship between TLC-2716 PK and PD, all subjects regardless of treatment assignment will be administered placebo capsule(s) on Day -1 to characterize the baseline daily variation of PD markers for subsequent comparison with changes that occur during dosing of TLC-2716 or PTM from Day 1 through 14. Additional details regarding dose escalation criteria are provided in Section 3.2.

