| 12-Lead ECG                                       | X                      | X                     |                | X k |       | X     |       |       |       | X     |          |        |            | X      |            | X                   | X                                           | X               |
| Randomization                                     |                        |                       | X              |                |       |       |       |       |       |       |          |        |            |        |            |                     |                                             |                 |
| Study drug or PTM administration n     |                        |                       | X n | X n | X     | X     | X     | X     | X     | X     | X        | X      | X          | X      |            |                     |                                             |                 |
| Plasma PK o                            |                        |                       |                | X              |       | X     |       |       |       | X     |          |        |            | X      | X          | X                   |                                             |                 |
| Plasma PD p                            |                        |                       | X              | X              |       |       |       |       |       | X     |          |        |            | X      |            |                     |                                             |                 |
| Biomarker: whole blood collection q    |                        |                       |                | X              |       |       |       |       |       |       |          |        |            | X      |            |                     |                                             |                 |
| Plasma NMR LipoProfile r               |                        |                       |                | X              |       |       |       |       |       |       |          |        |            | X      |            |                     |                                             |                 |

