**MAD Cohorts in Parts B and C:**

Days 1 and 14: Pre-dose ( $\leq 10$  minutes prior to dosing), and 2, 4, 6, and 12 hours post-dose

All post-dose timings above are relative to the morning dose for QD dosing or BID dosing. In the case of BID dosing in Part C, the 12 hours post-dose time point must be collected prior to the second daily dose of the study drug.

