**MAD Cohorts in Parts B and C:**

Days 1 and 14: Pre-dose ( $\leq 10$  minutes prior to dosing), 4 hours post-dose

Sampling time points may be modified by the sponsor based on emerging data and assay feasibility.

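### In the MAD cohorts, whole-blood ABCA1/ABCG1 and the NMR LipoProfile have no within-subject Day -1 time-matched sample, and the placebo subjects who could stand in as control fall outside the PD Analysis Set as written

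*Combined protocol and SAP*

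**What the plan says.** Protocol 1.3.1 gives all MAD subjects placebo on Day -1 "to characterize the baseline daily variation of PD markers for subsequent comparison with changes that occur during dosing of TLC-2716 or PTM". Sections 6.6.1 and 6.6.3 carry this through for plasma/serum PD and for exploratory biomarkers: both are drawn on Day -1 at 0, 2, 4, 6 and 12 h and again on Days 1, 7 and 14.

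The opening of 6.6.3 introduces two further assays. NMR appears among the possible uses of a separate serum aliquot, "including but not limited to IDOL, apolipoprotein C and E, and NMR-based lipid particle profiles". Whole blood for ABCA1 and ABCG1 mRNA follows, and that paragraph ends with the rule "The collection times on Day -1 must match the time of the collection on the day of dosing time points", within 5 minutes. The synopsis has the same rule, limited to MAD cohorts: "The collection times on Day -1 in MAD cohorts must match the time of the collection on the day of dosing time points".

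The detailed schedules differ. For both whole blood and the NMR LipoProfile, the MAD entry in 6.6.3 begins "Days 1 and 14: Pre-dose", with whole blood also at 4 h and NMR also at 2, 4, 6 and 12 h. In Table 6 the row "Biomarker: whole blood collection" and the NMR row, labelled plasma, have an empty Day -1 cell. The synopsis schedules and SAP Appendix 13-1 Table 2 agree with Table 6.

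On analysis, protocol 8.3.1.3 limits each PD Analysis Set to subjects who received TLC-2716, while protocol 8.8 summarises PD data by cohort and treatment group. SAP Section 2 defines no PD set. SAP Section 9 says only that absolute and percent change from baseline may be evaluated.

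**The concern.** The Day -1 placebo day separates a drug effect from the ordinary course of a day with meals. For whole blood and NMR it cannot do so, because nothing is collected. The only drug-free sample in an active subject is Day 1 pre-dose, so a within-day change in that subject mixes drug, meal and clock time. Section 1.3 itself notes that diet may affect serum lipids.

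At stake is the interpretation of a named exploratory endpoint (ABCA1/ABCG1, protocol 8.1.3) and of the lipoprotein particle profile. A Day -1 sample that was not taken cannot be recovered later. The wording also leaves a site unsure whether a Day -1 tube is required.

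**Working it through.** The plan states no figure on this point, so there is nothing to reproduce.

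**Coverage.** Count the sampling points after the first active dose (all of Days 1, 7 and 14 except Day 1 pre-dose), and how many have a Day -1 sample at the same clock time (protocol 6.6.1, 6.6.3, Table 6).

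| Marker | On-drug points | With Day -1 match | Of which post-dose | Post-dose matched |
|---|---|---|---|---|
| Plasma PD, exploratory | 4 + 5 + 5 = 14 | 14 | 12 | 12 |
| NMR LipoProfile | 4 + 5 = 9 | 0 | 8 | 0 |
| Whole blood | 1 + 2 = 3 | 0 | 2 | 0 |

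**What a within-day change contains.** In fed cohorts the meal starts 30 minutes before dosing (protocol 5.3.1) and the pre-dose sample is taken at most 10 minutes before dosing. The 0-to-4 h change therefore spans the post-meal period as well as the first hours of drug.

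**Which contrasts remain.**
- Day 14 pre-dose against Day 1 pre-dose, within subject: matched for clock time and meal. With once-daily dosing the Day 14 value is taken about 24 h after the previous dose, that is, at trough.
- Active against placebo at the same post-dose time: 8 against 2 in a cohort, or 8 against 5 × 2 = 10 with Part B placebo pooled.

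**Precision.** Protocol 8.10 says no reliable variability estimate exists, so these are multiples only. Let σ be the SD of one reading and ρ the within-subject correlation, with 0.5 and 0.7 assumed and equal SD in both groups. A change then has SD σ√(2(1−ρ)), which is 1.00σ or 0.77σ.

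| Contrast | SE formula | ρ = 0.5 | ρ = 0.7 |
|---|---|---|---|
| Change from Day 1 pre-dose, 8 active − 2 placebo | σ√(2(1−ρ))·√(1/8+1/2) | 0.79σ | 0.61σ |
| Same, 8 active − 10 pooled placebo | σ√(2(1−ρ))·√(1/8+1/10) | 0.47σ | 0.37σ |
| Change from same time on Day -1, 8 active only | σ√(2(1−ρ))·√(1/8) | 0.35σ | 0.27σ |

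Row 2 over row 3 is √(0.225/0.125) = 1.34, whatever ρ is. In units of the SD of the change, the 95% half-widths are 1.82 (8 v 2), 1.01 (8 v 10) and 0.84 (8 paired).

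Row 3 is not the SE of a drug effect. It is unrandomised and, at Day 14, includes two weeks of confinement and standard diet. Correcting it for pooled placebo returns the row 2 formula. Precision then improves only if readings at the same clock time correlate more closely than a pre-dose and a 4-h reading do; for example, 0.7 rather than 0.5 gives 0.37σ rather than 0.47σ.

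Day -1 sampling would also show the drug-free daily pattern in all 50 Part B subjects rather than in 10.

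**The case against.** The strongest case against has four parts.

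1. The design is randomised. Placebo subjects are sampled at the same times on Days 1 and 14, and subtracting their change removes shared meal and clock-time effects. This stands, so a reader who inferred that no drug-free time-matched control exists would be wrong. But the control is small, SAP Section 9 specifies no placebo correction, and the PD set read literally excludes these subjects.

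2. Day 14 against Day 1 pre-dose is a clean within-subject contrast. This also stands, for trough. Section 1.2.3 reports undetectable plasma levels 2 to 4 h after dosing in nonclinical work, so the clean contrast lies far from any peak in systemic exposure. The 4-h sample lies nearer to it and has no within-subject control.

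3. The matching sentence is generic and the exploratory biomarkers satisfy it. The whole-blood sentence sets time 0 at pre-dose on Day 1 or later, and every schedule agrees on Days 1 and 14, so the omission may be deliberate. The text is therefore ambiguous rather than impossible to follow. Nothing, however, limits the rule to the exploratory markers, and no reason is given for leaving the other two out.

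4. NMR might be run on the Day -1 serum aliquot, and the sponsor may modify sampling times. Both are possible; neither is a commitment, and the matrix (serum in 6.6.3, plasma in Table 6) is unsettled.

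**Conclusion.** The point holds as a gap in two exploratory markers. Neither has a within-subject Day -1 reference at any of its post-dose times (0 of 2 and 0 of 8). The remaining post-dose control is 2 placebo subjects per cohort, or 10 if Part B placebo is pooled, and the analysis plan does not secure their use. Primary safety and PK conclusions are unaffected.

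Two stronger readings are not supported. A reader might take whole-blood ABCA1/ABCG1 to be the trial's human test of liver selectivity. Section 1.2.2 uses peripheral whole blood that way for nonclinical data, and 1.3.2 selects doses to limit systemic effects, but no section gives the clinical assay that role. A reader might also set 0.79σ for 8 against 2 beside 0.35σ for a paired change and expect precision to more than double. At ρ = 0.5 the first figure is equally the SE of a raw 4-h contrast, which uses no baseline, and the second has no placebo correction. With pooled placebo and change from baseline on both sides, the figures are 0.47σ against 0.35σ (ρ = 0.5) or 0.37σ against 0.27σ (ρ = 0.7), and the smaller ones still omit the placebo arm. All these multiples rest on an assumed correlation and equal SDs.

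**What to change.** - **Sampling.** Add Day -1 whole blood at 0 and 4 h and NMR at 0, 2, 4, 6 and 12 h to Table 6, 6.6.3, the synopsis and SAP Appendix 13-1. PD blood is already drawn at those times. Alternatively, run NMR on the Day -1 exploratory serum aliquot. Either way, name one matrix for NMR.
- **Analysis.** Define post-dose change from the same clock time on Day -1. Show it for active and pooled placebo subjects, with the placebo-corrected difference.
- **Population.** Include placebo subjects in the PD Analysis Set (protocol 8.3.1.3) and add that set to SAP Section 2.
- **If Day -1 sampling is declined,** limit the matching sentence to the markers sampled on Day -1, and still make the population change and specify placebo-corrected change from Day 1 pre-dose.

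Cost: assay expense and a small extra blood volume at existing venepunctures. Part B needs 50 × 2 = 100 RNA and 50 × 5 = 250 NMR samples, with more if Part C runs MAD cohorts.

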### ***NMR LipoProfile***

**SAD Cohorts in Parts A and C:** None

**MAD Cohorts in Parts B and C:**

Days 1 and 14: Pre-dose ( $\leq 10$  minutes prior to dosing), and 2, 4, 6, and 12 hours post-dose

All post-dose timings above are relative to the morning dose for QD dosing or BID dosing. In the case of BID dosing in Part C, the 12 hours post-dose time point must be collected prior to the second daily dose of the study drug.

